## Abstract

**Background:**

Atopic dermatitis (AD) is a common pruritic inflammatory skin disease with increasing prevalence. It can manifest with many different clinical phenotypes; however, in its chronic stage, hyperpigmentation, excoriation, lichenification, and dryness are the main symptoms. *Jaungo* comprises two herbs, *Lithospermi* radix and *Angelica gigantis* radix, and three carrier oils, and is an approved herbal ointment for xerosis cutis in Korea. In past studies, we demonstrated that *Jaungo* had anti-inflammatory and antiallergic activity in in vitro and in vivo AD models; however, there are few relevant randomized controlled clinical trials on Jaungo in AD.

**Methods/design:**

A randomized, double-blind, placebo-controlled, single-center, phase IIa clinical trial was designed to investigate the safety, preliminary efficacy, and dose response of *Jaungo* in AD. The study protocol was approved by the Institutional Review Boards of the Kyung Hee University Korean Medicine Hospital (No. KOMCIRB-160617-HR-027) and the Korea Food and Drug Administration (No. 30907). The study aims to enroll 34 AD patients to be randomly distributed among three parallel groups: treatment 1, treatment 2, and the placebo group. Treatment group 1 applies *Jaungo* twice a day, while treatment group 2 applies *Jaungo* and the placebo ointment once a day, separately, and the placebo group applies the placebo ointment twice a day, for a total of 3 weeks each. Participants will be evaluated for eczema before and after the application of the ointments based on several parameters including the Eczema Area and Severity Index, the SCORing of Atopic Dermatitis Index, the Dermatology Life Quality Index, transepidermal water loss, total IgE level, eosinophil count, and IL-17, IL-22, and IFN-γ levels.

**Discussion:**

The trial is currently ongoing and the enrollment of subjects has been initiated. There is an urgent need to develop a drug for the treatment of dry, hyperpigmented, scaly, and thickened skin in chronic-stage AD. This study will determine the efficacy and safety of *Jaungo* in AD, providing evidence for specific AD symptoms treated by *Jaungo*.

**Trial registration:**

Clinical Trials.gov, identifier: NCT02900131. Registered on 2 September 2016. Korea Clinical Research Information Service, identifier: KCT0002060. Registered on 22 July 2016.

**Electronic supplementary material:**

The online version of this article (doi:10.1186/s13063-017-1920-9) contains supplementary material, which is available to authorized users.

## Background

Atopic dermatitis (AD) is a common pruritic inflammatory skin disease with increasing prevalence in industrialized countries. The prevalence of AD is 5–20% worldwide [1]. Altered immunity and reduced barrier function are fundamental to the development of AD [2], and the heterogeneous pathologic abnormalities observed in this patient population may contribute to the different clinical features seen in each patient. In the acute phase, AD manifests as erythema, microvesiculation, exudation, and crusting; however, in the chronic phase, the main symptoms of AD include hyperpigmentation, excoriation, and dryness. Additionally, severe itch can induce lichenification in the chronic stage owing to protracted rubbing of the skin [3].

The most effective therapy for AD includes short-term treatment of flares and a long-term maintenance approach to skin care designed to prevent or minimize flares [4]. Topical anti-inflammatory glucocorticoids (GCs) are standard therapy; however, long-term use of GCs carries the risk of side effects leading to the need for development of a therapeutic nonsteroidal topical agent.

*Jaungo* is an herbal ointment for xerosis cutis, frostbite, miliaria, anal fissures, and rhus dermatitis and approved by the Korea Food and Drug Administration (KFDA). It is composed of two herbs and three carrier oils: *Lithospermi* radix, *Angelica gigantis* radix, sesame seed oil, bees wax, and swine oil. Previous studies have demonstrated the anti-inflammatory and antiallergic activity of *Jaungo* in in vitro and in vivo AD models [5–7]. Additionally, a case series in 1999 reported the effect of *Jaungo* on AD [8], and two more recent studies reported the effects of *Jaungo* on both radiation dermatitis in breast cancer patients and cutaneous leishmaniasis [9, 10]. However, there are few relevant randomized controlled clinical trials on *Jaungo* for the treatment of AD.

The experimental focus of this trial is to evaluate the safety, preliminary efficacy, and dose response of *Jaungo* in patients having mild-to-moderate AD with hyperpigmentation, excoriation, lichenification, and dryness.

## Methods

### Study setting and design overview

This study will be conducted at the Kyung Hee University Korean Medicine Hospital in Seoul, Korea. The study is designed as a randomized, double-blind, placebo-controlled, single-center, phase IIa clinical trial to investigate the safety, preliminary efficacy, and dose response of *Jaungo* for treatment of AD. The study aims to enroll 34 patients with AD. Participants fulfilling the eligibility criteria will be selected and randomly distributed into three parallel groups: treatment 1, treatment 2, and the placebo group. Treatment group 1 applies *Jaungo* twice a day; treatment group 2 applies *Jaungo* and placebo ointments once a day, separately; and the placebo group applies placebo ointment twice a day, for a total of 3 weeks each. Participants will be evaluated for AD before and after applying ointment (see Figs. 1 and 2). A completed Standard Protocol Items: Recommendations for Interventional Trials (SPIRIT) Checklist for the trial is available (see Additional file 1).

**Fig. 1 Fig1:**
[figure not shown]
Study flow chart

**Fig. 2 Fig2:**
[figure not shown]
The schedule of enrollment, interventions, and assessments

## Eligible criteria

### Inclusion criteria

Patients will be eligible if they (1) have received a diagnosis of AD according to Hanifin’s and Rajka’s criteria, (2) are men or women aged 5 years to below 65 years, (3) have mild-to-moderate AD symptoms according to the objective SCORing Atopic Dermatitis (SCORAD) Index (score ≤40), and (4) have scores of excoriation, lichenification, and dryness in the SCORAD Index of at least 1 each, or a sum of 3 or more.

### Exclusion criteria

The exclusion criteria are as follows: (1) lesions with oozing, (2) oral administration of corticosteroids, immunosuppressants, or antibiotics 4 weeks prior to study entry, (3) administration of topical GCs, immunosuppressants, or antibiotics, or phototherapy, 2 weeks prior to study entry, (4) burn or trauma on the lesions, (5) allergic to *Jaungo*, or its components, including *Lithospermi* radix, *Angelica gigantis* radix, sesame seed oil, bees wax, and swine oil, (6) active skin diseases without AD, (7) renal or liver dysfunction, (8) other uncontrolled chronic diseases, (9) pregnancy or breastfeeding, (10) participation in other clinical trials within 1 month of enrollment, (11) inability to understand the written consent or to engage in this study due to mental impairment or other emotional or mental problems, and (12) judgment by experts that the potential subject’s participation is inappropriate.

Exclusion will be primarily based on information provided by the patient. Additionally, patients will undergo blood tests for aspartate aminotransferase (AST), alanine aminotransferase (ALT), blood urea nitrogen (BUN), creatinine (Cr), complete blood cell count/differential count (CBC D/C), erythrocyte sedimentation rate (ESR), human chorionic gonadotropin (hCG), and vital signs before the trial to ensure that the patients do not suffer from the listed diseases. A patient with liver dysfunction is defined as having ALT and AST values 2.5 times the upper limit of normal values (over 125 mg/dL for men and over 87.5 mg/dL for women). A patient with renal dysfunction was defined as having a serum Cr value over 2.0 mg/dL.

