### Intervention overview

Participants will apply *Jaungo* or placebo ointment for 3 weeks twice a day. The defined daily doses of *Jaungo* should be determined by the KFDA guidelines for specifications and analytical procedures of drug products; however, no pilot study has been performed. Therefore, we are utilizing the previously approved defined daily doses of *Jaungo* for treatment of xerosis cutis. Of note, *Jaungo* is given at a dose twice the strength of topical GCs; however, its anti-inflammatory activity is much less than that of topical GCs.

The fingertip unit (FTU) measurement will be utilized for participants to determine the required amount of the *Jaungo* to be used (Table 1). One FTU, approximately 0.5 g, is equal to the amount of ointment that is scooped out from the ointment pot with an adult fingertip (Fig. 3). The treatment area for the application of 1 FTU is equal to an area of the skin the size of a flat adult hand with fingers together. Participants will receive instructions for the specific amount of ointment to apply depending on their AD lesions.

**Table 1 Tab1:** Fingertip unit measurement (FTU) required to cover a specific skin area

Area of skin to be treated	Palm-sized	FTUs each dose (adults)	FTUs each dose (child)
A hand and fingers (front and back)	About 2 palms	2 FTUs (1 g)	1 FTUs (0.5 g)
Front of chest and abdomen	About 14 palms	14 FTUs (7 g)	7 FTUs (3.5 g)
Back and buttocks	About 14 palms	14 FTUs (7 g)	10 FTUs (5 g)
Face and neck	About 5 palms	5 FTUs (2.5 g)	4 FTUs (2 g)
An entire arm and hand	About 8 palms	8 FTUs (4 g)	5 FTUs (2.5 g)
An entire leg and foot	About 16 palms	16 FTUs (8 g)	9 FTUs (4.5 g)

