### Experimental medicine (*Jaungo*)

*Jaungo* ointment (Hanpoong Pharm and Foods, Co., Ltd., Wanju, Korea) was produced according to Korea Good Manufacturing Practice standards. *Jaungo* was approved for the treatment of xerosis cutis, frostbite, miliaria, anal fissure, and rhus dermatitis on 11 September 2014, by the KFDA. It is licensed to be applied to skin lesions one or more times per day.

*Jaungo* is composed of two herbs and three carrier oils: 72.7 mg of *Lithospermi* radix, 60.6 mg of *Angelica gigantis* radix, 60.1 mg of sesame seed oil, 242.4 mg of bees wax, and 18.2 mg of swine oil based on a total 1 g of ointment. It is a red-colored ointment with an herbal fragrance. The characteristic red color is due to the *Lithospermi* radix, and the distinctive aroma is due to the flavor components of bees wax and *Angelica gigantis* radix.

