### Placebo medicine

Hanpoong Pharm and Foods Co., Ltd., developed a homogenous ointment that is red in color with an herbal fragrance made with 698.1 mg sesame seed oil, 279.2 mg bees wax, 21 mg swine oil, 1.2 mg red iron oxide, and 0.5 mg ginseng-flavored extract based on a total 1 g of ointment. Substances, content, and preparative methods of the placebo ointment were approved by KFDA. The placebo ointment is very similar to the experimental medicine *Jaungo* in color, form, weight, and odor.

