### Blinding

To ensure blinding, a matched placebo ointment identical in color, texture, weight, and odor will be utilized and stored in a container identical to that of *Jaungo*. The *Jaungo* and placebo ointments will be labeled with a random number and “for morning use” or “for evening use” in an identical form. Treatment group 1 will receive two containers of *Jaungo*, one labeled with “for morning use” and the other “for evening use,” treatment group 2 will receive one container of *Jaungo* and one container of placebo ointment where one of the containers is labeled with “for morning use” and the other “for evening use.” The placebo group will receive two containers of placebo ointment, one labeled with “for morning use” and the other “for evening use.” The clinical pharmacist will supply *Jaungo*, the placebo ointment, or both to the patient depending on the patient’s assigned number. If the ointments are lost or destroyed, the clinical pharmacist will supply the patient with extra ointment labeled in an identical manner to maintain blinding.

In this trial, treatment distribution will remain unknown to the participants, investigators, outcomes assessors, statistician, and other staff until the end of the study. The randomization list and blinding codes will be kept strictly confidential. Access to the randomization list will be limited to the Clinical Research Organization (CRO) staff and the list will only be opened as a standard operating procedure. In the event that the randomization list has to be opened immediately, owing to an urgent situation pertaining to serious adverse events, the primary investigator must report the incident to the CRO. Participants will remain blinded to their respective treatment group until the final visit of the last randomized participant. The success of blinding will be assessed at each participant’s final visit. Researchers who are blinded to the distribution data will perform the outcome assessment. The blinding procedure will also be verified by the authorized CRO.

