## Discussion

AD is an eczematous disorder that manifests with erythema, microvesiculation, exudation and crusting in its acute phase, and dry, red, scaly skin in its chronic phase [3]. Treatment guidelines for AD focus on the acute stage of the disease which includes emollients and topical GCs. Topical GCs are the mainstay treatment for AD flare-ups, and in many cases AD can be controlled with topical corticosteroids or topical calcineurin inhibitors; however, some chronic AD patients require other treatment options due to GC side effects.

*Jaungo* is an approved herbal ointment for xerosis cutis, frostbite, miliaria, anal fissures, and rhus dermatitis in Korea. Topical application of *Jaungo* was found to have anti-inflammatory and antiallergic activity in our previous in-vivo and in-vitro studies [5–7]. Based on these findings, we designed a phase IIa clinical study to determine the clinical efficacy of *Jaungo* and its possible treatment mechanism in chronic-stage AD. This preliminary and exploratory study is critical for future confirmatory clinical trials, as no information exists for *Jaungo*’s application dose, frequency, and length of time that it should be administered in AD.

One of the important issues that we had to consider in this study was the blindness between the experimental drug, *Jaungo*, and the placebo ointment. *Jaungo* has a unique color and aroma. The characteristic red color is due to the *Lithospermi* radix, and its distinctive aroma is due to the flavor components of bees wax and *Angelica gigantis* radix. Red iron oxide and ginseng-flavored extract were used to manufacture the placebo ointment. Substances, composition, and manufacturing methods of the placebo ointment were approved by the KFDA. Additionally, to conceal the distribution data from researchers and participants, a web-based random number generator system was developed by an independent expert on web programming using Django Web Framework.

Limitations of this study are that it involves only 34 participants in a single center. This could potentially influence the generalizability of the study results. However, this study was designed to find the most responsive AD symptoms, to establish the proper application dose and frequency of *Jaungo*, and to identify the possible mechanism of action utilized by *Jaungo* for further study. In conclusion, this exploratory study will contribute to establishing *Jaungo*’s efficacy, safety, and dose response in AD.

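### The allergy exclusion covers only Jaungo's ingredients and leaves out two that are found only in the placebo ointment

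*Protocol article*

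**What the plan says.** The protocol article, under Exclusion criteria, prints twelve numbered exclusions. Number (5) concerns allergy to Jaungo or its components. It names the two herbs and three carriers, and the list closes with "radix, sesame seed oil, bees wax, and swine oil, (6) active skin diseases". The same section adds: "Exclusion will be primarily based on information provided by the patient". The laboratory tests listed there cover liver, kidney, blood count, ESR and pregnancy, and none of them tests for contact allergy. Criterion (12) leaves a residual right to exclude on expert judgment.

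Under Experimental medicine (Jaungo), the product is described as two herbs and three carrier oils, and the list ends "242.4 mg of bees wax, and 18.2 mg of swine oil based on a total 1 g of ointment". Under Placebo medicine, the ointment is sesame seed oil, bees wax and swine oil plus "1.2 mg red iron oxide, and 0.5 mg ginseng-flavored extract based on a total 1 g of ointment". The Discussion confirms the last two: "Red iron oxide and ginseng-flavored extract were used to manufacture the placebo ointment".

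The Blinding section shows who receives placebo. "The placebo group will receive two containers of placebo ointment", and treatment group 2 receives one container of Jaungo "and one container of placebo ointment where one of the containers is labeled" for morning and the other for evening use. Study setting and design overview gives the matching frequencies (placebo twice a day and once a day, respectively) and a duration of 3 weeks.

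**The concern.** An allergy exclusion should cover everything a randomised participant might be given. Here it is written around the active product alone. In criterion (5) the word for included components refers back to Jaungo, so it cannot be read to take in ingredients that only the placebo contains. Someone who knows they react to red iron oxide or to the ginseng-flavored extract passes criteria (1) to (11) as far as allergy goes, and has a roughly two-in-three chance of being assigned an ointment that contains it.

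What is at stake is the safety of that individual. Participants have a disease that the Background links to reduced barrier function, and they may be as young as 5 years. There is also a minor point of attribution. The known adverse events listed for Jaungo are allergic skin reactions such as rash and pruritus. A reaction to a placebo-only ingredient in treatment group 2 could be mistaken for one of these; in the placebo group it would count against placebo. The possible distortion of the adverse-event picture therefore has no single direction. Because the safety presentation is descriptive, that distortion is a remote possibility of unknown size.

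**Working it through.** The plan states no figure to reproduce. The check compares ingredient lists and then sizes the exposure.

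**1. Ingredients against the exclusion**

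| Ingredient | Jaungo (mg per g) | Placebo (mg per g) | Named in exclusion (5) |
|---|---|---|---|
| Lithospermi radix | 72.7 | none | yes |
| Angelica gigantis radix | 60.6 | none | yes |
| Sesame seed oil | 60.1 | 698.1 | yes |
| Bees wax | 242.4 | 279.2 | yes |
| Swine oil | 18.2 | 21 | yes |
| Red iron oxide | none | 1.2 | **no** |
| Ginseng-flavored extract | none | 0.5 | **no** |

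The placebo list is complete: 698.1 + 279.2 + 21 + 1.2 + 0.5 = 1000.0 mg. The printed Jaungo amounts sum to 72.7 + 60.6 + 60.1 + 242.4 + 18.2 = 454.0 mg, so completeness there rests on the article's statement that the product consists of two herbs and three carriers. The article attributes Jaungo's colour and aroma to its own ingredients, so nothing suggests that either placebo-only ingredient is in it.

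Share of the placebo: 1.2 / 1000 = 0.12% and 0.5 / 1000 = 0.05%, together 0.17%.

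**2. Other exclusions.** None of the remaining specific criteria mentions allergy to a placebo ingredient. Only (12) could apply, and it is discretionary.

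**3. Number exposed.** Randomization and allocation gives 34 participants at 1:1:1 with 11 to 12 per group, so the arms are 11, 11 and 12 in some order. The two arms that use placebo hold 11 + 11 = 22 or 11 + 12 = 23 people.

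**4. Illustrative amount.** Intervention overview states that "One FTU, approximately 0.5 g, is equal to the amount of ointment" taken up on a fingertip, and Table 1 gives 5 FTU (2.5 g) per dose for an adult's face and neck.

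- Per placebo application: 2.5 × 1.2 = 3.0 mg red iron oxide; 2.5 × 0.5 = 1.25 mg ginseng-flavored extract.
- Placebo group: 2 × 21 = 42 applications, giving 42 × 3.0 = 126 mg and 42 × 1.25 = 52.5 mg.
- Treatment group 2: 21 placebo applications, giving 63 mg and 26.25 mg.

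These totals describe exposure for one body area over the full 3 weeks. They do not measure allergic risk.

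**5. Expected number affected.** The article gives no allergy rate. Taking 0.1% to 1% for a known allergy to either ingredient, purely as an assumption: 22 × 0.001 = 0.022 to 23 × 0.01 = 0.23 persons.

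**The case against.** The best reply is that this is handled in substance. Exclusion rests mainly on what the patient reports; someone who reports such an allergy can be turned away under criterion (12), and someone who does not report it would not be caught by two more words in criterion (5) unless also asked. The screening form, which would settle whether the question is put, is not shown, and the article condenses a fuller protocol. The placebo's composition was approved by the KFDA, and the protocol by the review board and the KFDA. Participants may stop for side effects or worsening dermatitis, and adverse events, tolerability and the Draize score are assessed. The assumed allergy rate has no source in the article, and even so it gives well under one person.

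Part of this stands. Three weeks of exposure is a ceiling, because a reacting participant may be withdrawn. The practical gap depends on a form not available here, and the size is small under any plausible rate. The rest does not close the gap. Criterion (12) prompts nobody to ask about these ingredients. Product approval does not address an individual's known allergy. Withdrawal and adverse-event assessment act only after a reaction has occurred. Nor is this detail left to a fuller document: the article prints the numbered list and fixes the scope of (5) by naming its ingredients, and that scope is too narrow.

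**Conclusion.** The concern holds. As written, criterion (5) fully covers one of the two study ointments and misses two of the five placebo ingredients, while 22 to 23 of 34 participants apply the placebo. That conclusion rests only on the printed ingredient lists and the wording of the criterion, and is certain. The consequence is minor and less certain: the ingredients are 0.17% of the ointment, and 0.02 to 0.23 affected participants would be expected under an assumed allergy rate of 0.1% to 1%. It is a low-priority participant-safety correction. No effect on the efficacy results is claimed, and the finding concerns the written criterion, not the unseen screening form.

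**What to change.** Reword criterion (5) along these lines: *allergic to Jaungo, the placebo ointment, or any component of either, including red iron oxide and ginseng-flavored extract*. Keep the existing named ingredients, and make sure the screening interview or form asks about both additions; without the question the new wording would do little.

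The cost is one phrase in the eligibility list, a possible line on the screening form, and at most a rare extra screen failure. Sample size, endpoints and analysis are unchanged. Enrollment has begun, so the amendment would protect those still to be screened, and the same wording can carry over to the confirmatory trials foreseen in the Discussion.

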### Intervention overview

Participants will apply *Jaungo* or placebo ointment for 3 weeks twice a day. The defined daily doses of *Jaungo* should be determined by the KFDA guidelines for specifications and analytical procedures of drug products; however, no pilot study has been performed. Therefore, we are utilizing the previously approved defined daily doses of *Jaungo* for treatment of xerosis cutis. Of note, *Jaungo* is given at a dose twice the strength of topical GCs; however, its anti-inflammatory activity is much less than that of topical GCs.

The fingertip unit (FTU) measurement will be utilized for participants to determine the required amount of the *Jaungo* to be used (Table 1). One FTU, approximately 0.5 g, is equal to the amount of ointment that is scooped out from the ointment pot with an adult fingertip (Fig. 3). The treatment area for the application of 1 FTU is equal to an area of the skin the size of a flat adult hand with fingers together. Participants will receive instructions for the specific amount of ointment to apply depending on their AD lesions.

**Table 1 Tab1:** Fingertip unit measurement (FTU) required to cover a specific skin area

Area of skin to be treated	Palm-sized	FTUs each dose (adults)	FTUs each dose (child)
A hand and fingers (front and back)	About 2 palms	2 FTUs (1 g)	1 FTUs (0.5 g)
Front of chest and abdomen	About 14 palms	14 FTUs (7 g)	7 FTUs (3.5 g)
Back and buttocks	About 14 palms	14 FTUs (7 g)	10 FTUs (5 g)
Face and neck	About 5 palms	5 FTUs (2.5 g)	4 FTUs (2 g)
An entire arm and hand	About 8 palms	8 FTUs (4 g)	5 FTUs (2.5 g)
An entire leg and foot	About 16 palms	16 FTUs (8 g)	9 FTUs (4.5 g)

